### Secondary outcome measures

PCS of the SF-36™. The SF-36™ is the most frequently used generic health status measure worldwide that includes parameters such as pain and walking distance. It has been further developed to comprise physical (PCS) and mental health (MCS) component scores, thus easing the interpretation and cross-cultural comparison. It is a standardized questionnaire used to evaluate the patients’ health-related quality of life. It yields an 8-scale profile of functional health and well-being scores, as well as psychometrically based physical and mental health summary measures, and a preference-based health utility index. Thus, the SF-36™ is a good measure of primary endpoint. The patients' answers are scored and added together to yield a sum total. The SF-36™ PCS scores of the experimental and control groups will be compared to further quantify patient outcomes. In the subsequent follow-ups, the SF-36™ will be repeated to detect any clinical impairment and/or clinical or radiologic instability. This follow-up will continue for up to 3 years and then each year after surgery. In cases of impairment, X-ray is indicated at any point of time. In total, MCS and 8 individual dimensions and subscales of the SF-36™ (version 4.0) are used to confirm and clarify the primary outcome results.COMI questionnaire (2008 version) - a short, patient-oriented, multidimensional outcome instrument validated for patients with spinal disorders.X-rays will be taken after 6 weeks, and after 6, 12, 24, and 36 months. A further assessment will be performed every year. These are common intervals after surgical implantation without extraneous radiation. If adjacent instability is discovered on a X-ray, the clinical outcome will be reevaluated. The criteria for both radiologic ASD and adjacent instability are listed in the Appendix (definition of radiologic instability and Weiner’s classification). Experienced radiologists will evaluate the pre- and postoperative X-rays to calculate the score in Weiner’s classification. Furthermore, after 6 months, full-length X-rays of the spine will be taken to assess sagittal balance parameters (pelvic incidence, sacral slope, pelvic tilt, lumbar lordosis, C7 plum line, SVA). At each follow-up visit, bone fusion will be evaluated by indirect signs (screw loosening, implant failure, loss of reduction).Clinical ASD will be assessed (see definition in the Appendix).Work disability at the time of and after surgery, and duration until return to work. At each visit, patients will be asked to grade their disability, and whether or when they have returned to work.Inpatient mortality and mortality at 6 months.Surgery-related data (blood loss, length of incision, duration of surgery) will be taken from the surgical report.During the study, type and dose of pain medication administered to the patients will be documented. If the patient complaints of pain, the medication will be adjusted. The adjustment will be recorded on the CRF.Intraoperative and postoperative complication rate (e.g. implant failure- see Appendix under “Safety”)Adverse Events (AE) and Serious Sdverse Svents (SAE) will be monitored and documented throughout the study (see Appendix under “Safety” and “AE and SAE”).

### Sample size

On the basis of the data provided by Parker et al., the standard deviation is set at 11.3 points and the minimal clinically relevant difference at 11 for the changes in the Oswestry Disability Index (ODI) scores between the baseline and six months. In order to detect this clinically relevant difference between the two treatment groups, using a two-sided t-test with a significance level of 5% and a power of 80%, a total of 36 patients is required (18 per group) [30].

Assuming a drop-out rate of 10% until follow-up, 40 patients must be recruited for the study.

At a recruitment rate of 50% of the eligible patients and a rate of 60% of eligible patients in the screened population, 80 patients must be eligible among the 133 screened patients.

At a screening rate of approx. 100 patients in 12 months, duration of recruitment would be 16 months. To comply with the CONSORT requirements, we will provide a flow diagram of the participants. For each group, it will show the numbers of participants who were randomly assigned, received intended treatment, and were analysed for the primary outcome. Furthermore a diagram will illustrate for each group, losses and exclusions after randomization, together with reasons [31].

### Randomization

The patients will be assigned to the two treatment groups using an electronic randomization system provided by Aesculap®.

Balanced centre-stratified randomization with blocks of variable length. The randomization algorithm is implemented using statistical package SAS 9.2 and modified according to Dmitrienko et al. [32].

### Data management

At the study sites, the data will be entered online in a validated study database (eCRF) by trained personal. During data entry, plausibility tests will be carried out to tackle inconsistencies immediately. Later, a data manager will repeatedly check the data for completeness and plausibility and resolve the inconsistencies in concert with the centre. The central IT infrastructure will be provided by the ZKS.

The study database will be running on validated study software (MACRO). The study database itself will be validated before the data are entered. It will store all changes made to the data in an audit trail with a user and role concept adaptable to the specific study. The database will be integrated in a general IT infrastructure and security architecture with firewall and backup system. The data will be backed up daily.

### Data analysis

#### Primary target variable

The primary target variable is the functional change in the lumbar spine between baseline and 6 months as measured by the Oswestry Disability Index (ODI). The two-sided t-test for independent samples will be used as confirmatory test to compare the intervention group with the control group.

Analysis will be based on the intention-to-treat (ITT) principle. Consistency of the results will be verified by additional per-protocol (PP) subgroup analysis.

In addition, the results will be evaluated, focusing separately on each of the three diseases: degenerative disc disease, degenerative spondylolisthesis und spondylolisthesis. This applies to both the results from the ODI and to all other secondary target variables.

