### Outcome measures and assessments

#### Primary outcome measures

This investigation focusses on the subjective and objective clinical benefits for the patient. The ODI scores will be used to evaluate the functional outcomes after 6 weeks and after 6, 12, 24 and 36 months after surgery. The study hypothesis is:

The improvement in ODI scores from baseline to 6 months after surgery is clinically superior in the group with D-Rod (μRod) compared with the group without D-rod (μ).

To prove it, the following null hypothesis must be rejected: H0: |μRod - μ| ≤ MCID;

The alternative hypothesis is: H1: |μRod - μ| > MCID, with MCID assigning for minimum clinically important difference.

The hypothesis will be tested using a two-sided t-test for independent samples with a significance level of 5%.

In accordance with the recommendations of the European Agency for the Evaluation of Medicinal Products (EMEA), the patient’s bodily function may not be impaired if the only medical benefit is to relieve pain [25].

The ODI (cross-cultural adaption of the ODI version 2.1 for use with German-speaking patients) is a standardized, condition-specific questionnaire that gives a subjective percentage score of level of function (disability) in 10 everyday activities of daily living to be completed by patients rehabilitating from low back pain [25].

In the past, spine surgery investigations have focused on technical outcomes; now the main interest has turned to clinical outcomes [26, 27], measured by the ODI and SF-36™ , as in recent important trials (RCTs) [28, 29]. Radiologic findings are poor indicators of clinical outcome as it is unclear whether they correlate with clinical success.

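### The confirmatory test is an unadjusted t-test on ODI change that leaves out the stratifying centre and does not estimate the baseline effect: valid, but it gives away precision in a 40-patient trial

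*Protocol article*

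**What the plan says.** The confirmatory test is fixed in two places in the protocol article. Under Primary outcome measures: "The hypothesis will be tested using a two-sided t-test for independent samples with a significance level of 5" per cent. Under Data analysis, Primary target variable: "The two-sided t-test for independent samples will be used as confirmatory test to compare the intervention group with the control group". The endpoint is the change in ODI from baseline to 6 months, and neither section names a covariate.

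Under Randomization, allocation is described as "Balanced centre-stratified randomization with blocks of variable length"; there are two centres.

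Under Sample size, "the standard deviation is set at 11.3 points" for the ODI change, the difference to detect is 11 points, and the calculation is made "using a two-sided t-test with a significance level of 5% and a power of 80" per cent. This gives 18 per group, and then: "Assuming a drop-out rate of 10% until follow-up, 40 patients must be recruited for the study".

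**The concern.** Two pieces of baseline information are available for every randomised patient, and the confirmatory test makes poor use of them.

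- **Baseline ODI.** It is subtracted from the 6-month score, which fixes its regression coefficient at 1. If the true slope of 6-month ODI on baseline ODI differs from 1, subtraction leaves avoidable variance in the comparison. The estimate also moves with any chance imbalance in baseline ODI, which is likely to be noticeable with 18 per arm.
- **Centre.** Stratifying balances the arms within each centre. The two-sample t-test still counts any difference between centres as error, so its standard error is larger than the design warrants.

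At stake is precision in a trial that recruits only 40 patients. The test is written into the protocol, so an analysis plan that follows it would carry the loss forward.

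**Working it through.** **Inputs from the protocol article (Sample size):** SD of ODI change 11.3, difference 11, two-sided 5%, power 80%, 18 per group, 10% drop-out.

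**Inputs assumed, because the document does not give them:** correlation ρ between baseline and 6-month ODI, taken as 0.3 to 0.9; equal ODI SDs at the two visits; differences between centres of 0, 5 or 10 points. All power figures refer to a null of zero difference, the one under which the planned size reproduces.

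**1. The plan's own figure.** The non-central t calculation with 11/11.3 gives 17.58 per arm, rounded up to 18, so 36 in total. Power at 18 per arm is 81.0%. Drop-out: 36/0.9 = 40. Both stated figures reproduce.

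**2. Variance with and without adjustment.** With a common SD s:

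- change score: 2s²(1 − ρ)
- ANCOVA residual: s²(1 − ρ²)
- ratio: (1 + ρ)/2

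The ANCOVA residual SD is therefore 11.3 × √((1 + ρ)/2). The standard error of the treatment difference is SD × √(2/18) = SD/3. The t-test has 34 degrees of freedom (t = 2.032). ANCOVA with baseline and centre has 32 (t = 2.037).

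| Analysis | Variance ratio | SD | SE | 95% CI half-width | Power for 11 points | Evaluable total for 80% |
|---|---|---|---|---|---|---|
| Planned t-test | 1 | 11.30 | 3.77 | 7.65 | 81% | 36 |
| ANCOVA, ρ = 0.3 | 0.65 | 9.11 | 3.04 | 6.2 | 94% | 24 |
| ANCOVA, ρ = 0.5 | 0.75 | 9.79 | 3.26 | 6.6 | 90% | 28 |
| ANCOVA, ρ = 0.7 | 0.85 | 10.42 | 3.47 | 7.1 | 87% | 32 |
| ANCOVA, ρ = 0.9 | 0.95 | 11.01 | 3.67 | 7.5 | 83% | 34 |

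These formulas ignore the small extra variance from chance baseline imbalance. The simulation in step 5 includes it and gives ANCOVA power of about 93%, 90% and 85% for ρ = 0.3, 0.5 and 0.7. The case ρ = 0.9 was not simulated, and its two-point gain should be read as an upper figure.

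**3. Unequal SDs.** Let k be the 6-month SD divided by the baseline SD. The change-score variance exceeds the ANCOVA residual variance by (baseline SD)² × (1 − ρk)². This is never negative but is zero when ρk = 1, for example ρ = 0.8 and k = 1.25. In that case, and with no centre difference, adjustment only costs its two degrees of freedom: the half-width goes from 3.767 × 2.032 = 7.65 to 3.767 × 2.037 = 7.67.

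**4. Chance baseline imbalance.** With equal SDs, s = 11.3/√(2(1 − ρ)), which is 9.55, 11.3 and 14.59 for ρ = 0.3, 0.5 and 0.7. One standard error of baseline imbalance is s/3. It shifts the change-score difference by (1 − ρ)s/3, or about 2.2, 1.9 and 1.5 points. ANCOVA removes this shift.

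**5. Centre.** Simulation with 18 per arm balanced within centre, ρ = 0.3 to 0.7 and 8,000 trials per setting:

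| Centre difference (assumed) | t-test type I error | t-test power |
|---|---|---|
| 0 | about 5% | 80–81% |
| 5 points | 4.0–4.5% | 79–81% |
| 10 points | 3.3–3.5% | 75–76% |

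The adjusted model stays near 5% throughout, and its power does not depend on the centre difference.

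**The case against.** The strongest reply is that nothing here is wrong. The t-test is valid under randomisation, the sample size was calculated for exactly this test, and it reproduces. By its own inputs the trial is not underpowered. That stands, and it limits the point to efficiency.

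The size of the gain is also open. The document gives no correlation, no visit-specific SD and no centre effect. The gain is small at ρ = 0.9 and vanishes when ρk = 1. That stands too, and is why a range is shown.

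Four stronger readings are tempting, and the document does not support them:

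- **That baseline ODI is ignored.** It is subtracted in every change score; it is only not estimated as a covariate. Regression to the mean affects both randomised arms and does not bias their comparison in expectation.
- **That leaving out centre inflates the type I error.** The simulation shows the opposite: where centres differ, the test is conservative.
- **That the promised intention-to-treat analysis is not delivered and 10% of patients leave the comparison.** The article states "Analysis will be based on the intention-to-treat (ITT) principle" and nowhere excludes patients without a 6-month score. The step from 36 to 40 is a planning allowance and does not define an analysis set. A t-test can follow imputation, and the handling of missing values is commonly left to the full protocol or analysis plan, which is not shown.
- **That most drop-outs will have a 6-week ODI to use instead.** A 6-week ODI is scheduled, but nothing says when drop-outs are expected.

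**Conclusion.** The point holds as an efficiency weakness that is fixed in the text and worth correcting before data are seen. Under equal SDs and a zero-difference null, the planned test gives away about 2 to 13 percentage points of power (ρ from 0.9 to 0.3), equivalent to 2 to 12 of the 36 evaluable patients. It gives away up to about 6 further points if the centres differ by 10 ODI points. The direction is safe: in large-sample terms adjustment cannot increase the residual variance, and its worst case is the loss of two degrees of freedom. The amount is uncertain because the correlation, the SD ratio and the centre difference are all assumed.

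The Primary outcome measures section also states a null hypothesis shifted by the minimum clinically important difference. That is a separate matter, and the power figures here do not describe that hypothesis.

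**What to change.** In both Primary outcome measures and Data analysis (Primary target variable), name as the confirmatory analysis a linear model (ANCOVA) of 6-month ODI on treatment, baseline ODI and centre. The treatment coefficient is tested two-sided at 5% and reported with its 95% confidence interval. Keep the two-sample t-test on change as a sensitivity analysis. Leave 36 evaluable and 40 recruited as they are; under the planning SD they become a conservative size.

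A repeated-measures model that also uses the 6-week ODI is an option, but this point does not depend on it, and it would need more parameters than the ANCOVA.

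The cost is a change of wording in two sections and two degrees of freedom. No additional data or visits are needed.

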## Methods and design

The study is a randomized, parallel-group, therapy-controlled trial in a clinical setting at two university hospitals. Outpatients presenting with degenerative disc disease, symptomatic facet joint arthrosis or spondylolisthesis will be assessed for inclusion. They will be asked to give an informed consent and will be randomized before surgery. Follow-up examinations will take place immediately after surgery, and after 6 weeks, 3 months and 6 months, the total duration of the study. Furthermore data will be assessed after 12, 24 and 36 months for a supplemental investigation. A further assessment will be performed every year, as it may be impossible to pronounce on ASD after 36 months.

This trial has received the approval of the ethics committee of the medical faculty of the University of Cologne under the reference number 12–231. The Clinical Trial Centre of the University of Cologne will monitor and manage the data. The research will be carried out in compliance with the Helsinki Declaration [21].

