### Participants and recruitment

Outpatients over 30 years of age presenting with degenerative disc disease, facet joint arthrosis or spondylolisthesis, and indications for monosegmental lumbar spine fusion will be eligible for trial inclusion. Radiologic inclusion criteria are summarized in the Appendix.

The presence of radiologic degeneration of the adjacent segment (Pfirrmann grades II-IV in MRI findings [22]) without signs of instability will be a condition for inclusion. The definition of radiologic and clinical instability and the other inclusion criteria are summarized in the Appendix.

Experienced spine surgeons will approach and recruit the study subjects. The number of patients who undergo primary monosegmental fusion in the departments is estimated at 200 per year and the number of recruited patients at 20 per year per centre.

Patients participating in parallel interventional studies as well as patients with lumbar scoliosis (>25° cobb angle), spondylolisthesis Meyerding IV, adjacent segment instability and/or radiologic ASD worse than Fujiwara grade II or Pfirrmann grade IV [22, 23] will be excluded from this study. This also applies to patients with indication for multilevel fusion. The other exclusion criteria are summarized in the Appendix.

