## Appendix

### Inclusion criteria

Informed consentLegal capacityAge ≥ 30 yearsIndication for monosegmental lumbar spine fusion L2-S1 with osteochondrosis Modic grades I-IIIIndication for monosegmental lumbar spine fusion L2-S1 with spondylolisthesis Meyerding grades I-III (signs of instability in the functional x-rays and a.p. and lateral view; see definition of radiologic instability).Indication for monosegmental lumbar spine fusion L2-S1 with symptomatic facet joint arthrosis or degenerative disc disease (>Fujiwara grade II [23] or > Pfirrmann grade IV [22])Radiologic signs of degeneration in the adjacent segment of the intended fusion without signs of instabilityDefinition of adjacent segment degeneration (MRI)Pfirrmann [22] grades II-IVGrade I: Homogeneous bright white structureGrade II: Inhomogeneous white structure, possible horizontal bandsGrade III: Clear distinction between annulus and nucleusGrade IV: Non-collapsed disk spaceGrade V: Collapsed disk spaceDefinition of radiologic instability (x-ray: a.p. and lateral view, extension and flexion):Spondylolisthesis >4 mm (anterior or posterior translation) [3]Segmental kyphosis >10° [3]Rotatory hypermobility >15° [14]Complete collapse of the disc [3]Lateral translation >3 mm [14]Disc wedging >5° [14]Deterioration in Weiner’s classification of 2 or more grades in the follow-up evaluation [1, 27]

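### The three disease groups named for the by-disease evaluation do not match the diagnoses enrolled: facet joint arthrosis has no group, and degenerative spondylolisthesis fits two

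*Protocol article*

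**What the plan says.** Under Data analysis, Primary target variable, the protocol article sets one confirmatory comparison: a two-sided t-test on the change in ODI from baseline to 6 months, by intention to treat. It then adds an evaluation "focusing separately on each of the three diseases: degenerative disc disease, degenerative spondylolisthesis und spondylolisthesis". The scope is wide: "This applies to both the results from the ODI and to all other secondary target variables".

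Enrolment is described differently:

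- Methods and design: "Outpatients presenting with degenerative disc disease, symptomatic facet joint arthrosis or spondylolisthesis will be assessed for inclusion".
- Participants and recruitment: patients "presenting with degenerative disc disease, facet joint arthrosis or spondylolisthesis, and indications for monosegmental lumbar spine fusion will be eligible for trial inclusion". The abstract names the same three diagnoses.
- Appendix, Inclusion criteria: three separate indications for fusion. One is osteochondrosis Modic I-III. One is spondylolisthesis Meyerding I-III, not divided by type. The third is "Indication for monosegmental lumbar spine fusion L2-S1 with symptomatic facet joint arthrosis or degenerative disc disease", with a grading threshold.

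The Randomization section stratifies by centre and does not mention diagnosis. The Sample size section gives 36 patients (18 per group), with 40 to be recruited, and no breakdown by diagnosis.

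**The concern.** The analysis section speaks of three diseases as a closed list, but it is not the list of diseases that patients enter with. One enrolled indication, facet joint arthrosis, is absent. One entry, degenerative spondylolisthesis, is a kind of another entry, spondylolisthesis, and no rule separates them. Osteochondrosis, a criterion in its own right in the appendix, is not placed either.

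An analyst who follows the text would leave some patients out of every by-disease table and could count others twice. An analyst who repairs the list has to choose a grouping that the protocol does not state. Blinding is not attempted in this trial, so that choice could be made by someone who has seen allocation and outcomes. The appendix indications are also not stated to be mutually exclusive, so a patient with several findings has no assigned home. Health care providers, whose interest the Discussion mentions, could then read a diagnosis-specific result that does not describe the patients its label suggests.

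**Working it through.** **Step 1. Set the lists side by side.**

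| Diagnosis | Enrolled (abstract, methods, recruitment) | Appendix criteria | By-disease group |
|---|---|---|---|
| Degenerative disc disease | yes | yes, in one criterion with facet arthrosis | yes |
| Facet joint arthrosis | yes | yes, in one criterion with disc disease | none |
| Spondylolisthesis | yes, undivided | yes, Meyerding I-III, undivided | yes, undivided |
| Degenerative spondylolisthesis | not named separately | not named separately | yes, as a further group |
| Osteochondrosis Modic I-III | not named | yes, own criterion | none |

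The by-disease list is neither exhaustive nor mutually exclusive. No other section gives a mapping.

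**Step 2. Reproduce the plan's sample size.** Inputs from the Sample size section: "the standard deviation is set at 11.3 points and the minimal clinically relevant difference at 11", two-sided 5%, power 80%.

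- Normal approximation: n per arm = 2 × (1.960 + 0.842)² × (11.3/11)² = 16.6, rounded up to 17.
- Non-central t: 17.58, rounded up to 18 per arm, total 36, as stated. Power at 18 per arm is 81.0%.
- Drop-out: 36 / 0.90 = 40, as stated.

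**Step 3. What a disease group could show.** The article gives no subgroup sizes, so these are assumed. The same difference, SD and alpha are kept, with equal arms within each group.

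| Patients per arm in the group | Power for 11 points (t) | Difference detectable with 80% power |
|---|---|---|
| 3 | 15% | 34.7 |
| 4 | 21% | 26.9 |
| 5 | 27% | 22.9 |
| 6 | 33% | 20.3 |
| 7 | 39% | 18.4 |
| 8 | 44% | 17.0 |
| 9 | 49% | 15.9 |
| 10 | 54% | 15.0 |

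Six per arm is 18/3 and holds only if three equal, non-overlapping groups contain every patient. Four equal groups would give 18/4 = 4.5 per arm.

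The 95% confidence interval half-width is t(0.975; 2m − 2) × 11.3 × √(2/m), with m patients per arm:

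- m = 3: 2.776 × 11.3 × 0.816 = 25.6 points
- m = 6: 2.228 × 11.3 × 0.577 = 14.5 points
- m = 10: 2.101 × 11.3 × 0.447 = 10.6 points

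At 6 per arm the interval reaches further on each side than the 11 points that the trial is designed to detect.

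**The case against.** The strongest defence is that the list is a slip with an obvious repair. The appendix places "symptomatic facet joint arthrosis or degenerative disc disease" in a single criterion, so pooling the two may be intended. Naming degenerative spondylolisthesis beside spondylolisthesis may mean degenerative against other types. The untranslated conjunction in the list suggests hurried translation. The article condenses a fuller protocol, and a statistical analysis plan may settle the groups. Both readings are plausible, but neither is stated, and the problem is a stated list that disagrees with the article's own eligibility text rather than a missing detail. A later plan must either follow the list or depart from it.

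Other parts of the defence stand and limit the point. A reader might infer that the plan runs a significance test in each disease. The text says that results will be evaluated, in addition to one confirmatory test; it specifies no subgroup test and does not say whether the evaluation is descriptive.

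A reader might go on to count 12 scores (ODI, PCS, MCS, eight SF-36 scales, COMI) in three groups as 36 tests, and compute 1 − 0.95³⁶ = 84% for at least one false positive. The documents do not support that figure. The 36 tests are not specified, the scores come from the same patients and partly from the same questionnaire, and the groups overlap as written.

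Nor do the documents support taking 6 per arm as a fact, or asking for an interaction term in an adjusted ODI model. The planned primary analysis is an unadjusted t-test, and the plan does not claim to show that effects differ by diagnosis.

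**Conclusion.** The by-disease evaluation is wrong as written. Its groups contradict the enrolled diagnoses, leave facet joint arthrosis without a group, and let degenerative spondylolisthesis fall in two. This rests on the text alone and needs no assumption about numbers.

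The numerical part is conditional: with 3 to 10 patients per arm per group, equal arms, and the planning SD of 11.3 holding within each disease, power for 11 points runs from about 15% to 54%. Even with the groups repaired, such results cannot support a claim that the device works, or does not work, in one disease.

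A reader might infer that facet joint arthrosis patients are lost to the trial's main result. They are not: the confirmatory ODI comparison covers the intention-to-treat population whatever the diagnosis, and neither it nor the sample size is affected. The point should be corrected, but it does not threaten the primary conclusion.

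**What to change.** Replace the list in the data analysis section with mutually exclusive, exhaustive groups that match enrolment: degenerative disc disease, facet joint arthrosis and spondylolisthesis. State explicitly which of these takes the patients enrolled under the osteochondrosis criterion. If a split of spondylolisthesis by type is wanted, define it so that no patient is in both parts.

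Assign each patient to one main indication, recorded before randomisation, so that the grouping cannot depend on outcomes. State that by-disease results for the ODI and the secondary variables are exploratory, and report them as estimates with confidence intervals and the number of patients per arm.

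The cost is a wording change and at most one pre-randomisation field; if the case report form already records a single main indication, no new field is needed. Sample size, randomisation and the confirmatory test stay as they are.
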